### Sample size calculation

In order to assess the effectiveness of the StroCare intervention, the two prospective groups will include all patients insured with the health insurance BARMER who will be hospitalised in one of the three participating clinics over a period of 24 months for stroke treatment and have given their written consent. Previous studies showed moderate to large effects of similar interventions on health-related quality of life with standardized mean differences (Cohen’s *d*) between treatment and control groups ranging from 0.2 to 0.6 [8, 12]. We aim to identify a moderate effect (Cohen’s *d*=0.3) of the intervention on patient’s experienced health-related quality of life. With a power of 80% and an alpha error of 0.025 (adjusted for two primary endpoints, the two subscales of the PROMIS-10), a sample size of *N*=213 patients per group (426 in total) will be needed. Accounting for an expected dropout rate of 10% results in a necessary sample size of 235 per group (470 in total). In the past few years, approximately 600 patients insured with BARMER with a diagnosis of stroke were treated annually in the three participating clinics. In the planned time frame of 24 months we thus expect to enroll the planned number of 426 patients if 39% of 1200 participants participate.

For the qualitative interviews it is indicated that on average 12 interviews are sufficient to reach theoretical saturation [13]. Thus, the planned sample size of a maximum of 21 patients enrolled in the intervention group and 20 employees of different departments (doctors, nurses, and IT staff) represents a meaningful basis for the investigation of the experience gained during the implementation.

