### Outcome measures

#### Effectiveness

In order to assess the effect of intervention, patient-reported outcomes will be surveyed measuring health-related quality of life (Fig. 3). They will be measured 12, and 24 months after baseline, using the questionnaire “Patient Reported Outcome Information System 10-Question Short Form” (PROMIS-10). The PROMIS-10 is a standardized questionnaire and consists of two scales measuring mental health and physical health [14], respectively, which will serve as the two primary outcomes. For evaluation of the PROMIS-10, at first a sum score and afterwards a t-score with standardized t-values is calculated. Reference of M ± SD= 50 ± 10 regards to a sample of healthy American subjects.

Additionally, the secondary outcome of depression and anxiety symptoms will be measured at all time points, using the “Patient Health Questionnaire-4” (PHQ-4) [15]. This questionnaire entails the two dimensions, depressive and anxiety symptoms, with two items each. The sum score ranges from 0 to 6 in each dimension. A score of 3 or higher indicates a potential anxiety or depression. The patient’s functional status will be assessed by the modified Rankin Scale questionnaire (smRSq) [16]. The scale of the smRSq ranges from 0 (“no symptoms”) to 6 (“death”). The outcomes of overall survival and stroke recurrence will be measured with the ICHOM-Standard set for Stroke [11]. The ICHOM-Standard Set for Stroke was developed under the coordination of the International Consortium for Health Outcomes Measurements (ICHOM) and measures a range of patient-reported outcomes from functionality to general health status. Further secondary outcomes are: utilization of health care services, patient’s waiting time between treatment phases, success in regaining target values of relevant risk factors (blood pressure, LDL-cholesterol, HbA1c) and costs. These parameters will be measured via the medical patient record and the rehabilitation portal. Also, a sociodemographic questionnaire will be used, measuring age, gender, living situation, partnership, vascular and non-vascular comorbidities.

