### Data analysis

#### Analysis of effectiveness outcomes

The structural equality of the control and intervention groups at baseline will be examined to detect imbalances, using descriptive statistical analysis.

In order to evaluate the intervention effect on the two primary outcomes at the 12-months follow-up, data will be analyzed using linear mixed models. In the fixed part of the model, exposure to the intervention (StroCare vs usual care) will be included as the independent variable of interest. Potential confounding variables will be added as fixed effects in case of baseline imbalance, including demographic characteristics, stroke type and severity of stroke symptoms, as well as vascular and systemic features. The random effects part of the model will include variance parameters for the intercept and for the treatment effect across the participating clinics, respectively. Findings regarding the primary outcomes with an alpha error rate below 0.025 will be considered statistically significant (Bonferroni adjustment for two outcomes).

The primary outcome at the 24-months follow-up and the secondary outcomes will be analyzed using similarly structured models. In the case that data are not normally distributed, generalized mixed models will be applied. Findings regarding the secondary outcomes with an alpha error rate below 0.05 will be considered statistically significant.

Parameter estimates will be reported with 95% confidence intervals. Missing values will be handled using multiple imputation.

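### The two primary PROMIS-10 scales are tested at 0.025 but reported with 95% intervals, so an interval can exclude zero on a primary endpoint that the plan calls non-significant

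*Protocol article*

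**What the plan says.** The section on effectiveness outcome measures names two primary outcomes: the PROMIS-10 "consists of two scales measuring mental health and physical health [14], respectively, which will serve as the two primary outcomes".

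The section on analysis of effectiveness outcomes gives the decision rule for them: "Findings regarding the primary outcomes with an alpha error rate below 0.025 will be considered statistically significant (Bonferroni adjustment for two outcomes". Secondary outcomes are judged at 0.05. The same section then sets one interval level for everything: "Parameter estimates will be reported with 95% confidence intervals". No other level is given for the primary comparisons.

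The sample size section is built on the same test level: "With a power of 80% and an alpha error of 0.025", with the reason given as adjustment for the two PROMIS-10 subscales. The target effect is stated as "We aim to identify a moderate effect (Cohen’s *d*=0.3) of the intervention", and the result as "a sample size of *N*=213 patients per group (426 in total) will be needed".

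**The concern.** Test level and interval level are both fixed in one section, and they differ. This is therefore not a detail left to an unseen analysis plan. A reader of the results will treat an interval that excludes zero as evidence of an effect. If that interval belongs to a primary scale with p between 0.025 and 0.05, the results table and the plan's own verdict on the endpoint will disagree, and the table is the part most readers will remember.

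Joint coverage raises the same issue. Two 95% intervals together guarantee only 90% coverage (1 − 2 × 0.05). Two 97.5% intervals guarantee 95% (1 − 2 × 0.025), which is the family-wise level that the Bonferroni rule controls.

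**Working it through.** **Inputs.** From the sample size section: d = 0.3, alpha 0.025 per scale, power 80%, 213 per group before the dropout allowance. From the analysis section: 0.025 for the primary outcomes and 95% intervals. From the outcome section: reference T-score SD of 10 (the trial's own SD is not given, so using 10 is an assumption). The correlation between the two scales is not given; a range of 0 to 0.9 is assumed.

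**1. Reproducing the plan's figure.** The article does not state sidedness.
- Two-sided 0.025, normal formula: n = 2(2.241 + 0.842)² / 0.3² = 211.2, so 212 per group. The exact t-test calculation gives 213, with power 80.1%.
- One-sided 0.025: 2(1.960 + 0.842)² / 0.3² is about 174.4, so 175 per group, which does not fit.

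The trial is therefore sized on a two-sided 0.025 test. Sample size and decision rule agree; the interval level is the part that does not fit.

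**2. Where interval and decision part.** A 95% interval excludes zero when |z| > 1.960. The primary decision needs |z| > 2.241. They disagree when |z| lies between these values, that is for 0.025 ≤ p < 0.05. The reverse cannot happen: if p < 0.025, the 95% interval always excludes zero.

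**3. On the effect scale.** z = d × √(213/2) = d × 10.32.
- Lower limit: 1.960 / 10.32 = 0.190
- Upper limit: 2.241 / 10.32 = 0.217
- With SD 10: about 1.90 to 2.17 T-score points

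**4. How often.** At d = 0.3 the mean of z is 0.3 × 10.32 = 3.096. The chance of landing in the zone is Φ(2.241 − 3.096) − Φ(1.960 − 3.096), which is 6.8%; the opposite tail is negligible. This equals power at 0.05 minus power at 0.025: 87.2% − 80.4%. The same calculation gives 11.2% at d = 0.2 and, counting both tails, 2.5% at d = 0. For at least one of the two scales at d = 0.3, simulation (2 million draws) gives 13.2% at correlation 0 and 12.0% at 0.9.

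**5. Width of a matching interval.** 2.241 / 1.960 = 1.14, so a 97.5% interval is 14% wider.

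**6. Holm as an alternative test** (same simulation, d = 0.3 on both scales, 213 per group):

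| Correlation | Per scale, Bonferroni → Holm | Both scales, Bonferroni → Holm | At least one, either method |
|---|---|---|---|
| 0 | 80.4% → 85.9% | 64.7% → 75.6% | 96.2% |
| 0.5 | 80.4% → 84.9% | 69.3% → 78.3% | 91.6% |
| 0.9 | 80.4% → 83.6% | 75.5% → 81.9% | 85.4% |

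The trials that Holm adds to the both-scales column are those where one scale has p < 0.025 and the other has p from 0.025 to just under 0.05. With 97.5% intervals, the second scale would be declared significant while its interval covers zero. This occurs in 10.9%, 9.0% and 6.4% of trials at the three correlations (for example 75.64 − 64.70 = 10.94). Holm with 95% intervals still leaves a mismatch in 2.2% to 5.6% of trials over the range 0 to 0.9.

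**The case against.** The strongest defence is that the plan never says significance will be read from an interval. The decision rests on an explicit 0.025 threshold, the interval sentence covers primary, secondary and 24-month estimates alike, and a 95% interval is a correct marginal interval for a single estimate. The plan claims no simultaneous coverage. All of this is true, and it confines the point to reporting. It does not remove the point: the article gives no warning that the primary intervals are unadjusted, and a reader will set them beside a verdict reached at a stricter level.

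Three stronger readings are tempting and are not supported.

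- A reader might infer that the family-wise error is inflated. It is not. The two 12-month tests at 0.025 hold it at or below 5%, whatever intervals are printed.
- A reader might infer that choosing Bonferroni is itself a mistake that gives away power for nothing. Bonferroni is valid, prespecified and consistent with the sample size. The article states no objective of succeeding on both scales, and Holm leaves the chance of succeeding on at least one unchanged. Nor is Holm free of cost: Bonferroni has simple matching intervals and Holm has none as simple.
- A reader might infer from the analysis section's wording about the 24-month follow-up that there are more than two primary tests. The abstract places the primary outcome at 12 months, so calling the 24-month scales secondary would only clarify.

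It is also fair to object that the frequencies are not those of the planned model. They come from a two-group normal comparison, whereas the plan has a random intercept and a random treatment effect across clinics. This objection stands as a limit on the figures.

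**Conclusion.** The point holds as a reporting mismatch of modest size. For any primary p-value from 0.025 to just under 0.05, the plan as written would print an interval excluding zero on an endpoint it declares non-significant. That follows from the two stated levels alone, provided test and interval come from the same estimate, standard error and reference distribution.

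The size depends on assumptions: 213 analysed per group, a two-sided normal test and no clinic random effects. On these, the chance per scale is about 7% at the design effect and about 11% at d = 0.2, the low end of the range of earlier effects cited in the sample size section. The power figures in the working are best case for the same reason, and they also depend on the assumed correlation. Test validity and sample size are not in question.

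**What to change.** Keep Bonferroni and change the interval sentence: 97.5% confidence intervals for the two 12-month primary PROMIS-10 comparisons, 95% intervals for all other estimates. Interval and decision then agree in every case. The cost is one sentence and primary intervals 14% wider; the sample size does not change.

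An optional alternative is to test with Holm: the smaller p-value at 0.025 and, if that is significant, the other at 0.05. At the design effect this adds about 3 to 5 points of power per scale and 6 to 11 points for both scales, and nothing for at least one. If Holm is chosen, keep the 95% intervals and state that they are unadjusted and that the decision rests on the Holm p-values. Do not pair Holm with 97.5% intervals.

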#### Analysis of the process outcomes

The audio recordings of the conducted interviews will be transcribed. Qualitative data will be analyzed using qualitative content analysis based on P. Mayring [19]. A deductive-inductive approach will be used with deductive categories derived from literature and inductive derived from the analysis of the qualitative interviews. This method was chosen for its structuring and at the same time adaptable approach.

#### Analysis of the economic outcomes

We will employ both two-part (binomial, gamma) and generalized linear models (gamma distributed outcome) to analyze health care costs, because these models can incorporate the special features of cost distributions – i.e. right skewed distributions that contain a large proportion of zero values [20]. Cox-regression or frailty models as well as generalized linear models will be considered to analyze secondary outcomes such as rehospitalizations, the duration of hospital stays or the utilization of specific services.

### Perspective

This study combines different aspects of health care (primary contact, outpatient managed care, case management, coverage of costs by the health insurance company and an electronical allocation of capacities) in order to improve managed care of stroke patients. The study will not only provide information on the tested intervention but is likely to be helpful for stakeholders and researchers implementing and evaluating complex interventions in stroke care in general. The StroCare interventions will be established at three acute-care clinics with different care structures including five rehabilitation clinics in northern Germany and a nationwide health insurance company. Thus, the health care system will have an evaluated reference model at its disposal for transfer to other regions as well as organizational structures and processes.

## Data Availability

Data will be made anonymous by the research staff during transcription. After completion of the project, the research data/primary data will be stored for another 10 years on durable and secure carriers of the project group in accordance with the proposals for safeguarding good scientific practice of the DFG – German Research Foundation (www.dfg.de). Data evaluation will be carried out by the research staff and no personal data will be published or passed on to third parties. Upon reasonable request that includes a methodologically sound proposal for the usage of data that is also approved by the responsible review committee data may be shared.

## Abbreviations

StroCare: Inter-sectoral, coordinated and evidence-based stroke care
PROMs: Patient-reported outcomes
ICHOM: International Consortium for Health Outcomes Measurements
ICHOM-SSS: ICHOM Standard Set for Stroke
PROMIS-10: Patient Reported Outcome Information System 10-Question Short Form
PHQ-4: Patient Health Questionnaire-4
UKE: University Medical Center of Hamburg-Eppendorf
